## Abstract

The default use of masculine morphology to refer to all genders in Arabic-speaking countries is largely unquestioned and widely accepted. However, research on masculine generic morphology in other gender-marked languages has shown that this can create an over-representation of men and a male-bias in perception. Given the extensive use of default masculine grammatical gender in the context of job recruitment, education, and formal communication where women are typically underrepresented and men overrepresented, this widely accepted notion needs to be investigated. The primary aim of this research is to understand how grammatical gender in Arabic mediates occupational expectations based on the language currently used in job recruitment in Arabic speaking countries. Specifically, the study explores how the use of default masculine grammatical gender can create a male-bias in perception. The secondary aim of this research is to test whether gender-inclusive language can reduce this male-bias in perception and instead increase the accessibility, activation, and retrieval of exemplars related to other gender minorities (i.e., reduce male-bias in perception). This is achieved through a novel prompted speech production experiment, based on an adaptation of the popular board game ’Taboo’ where participants are asked to describe role nouns presented (e.g., *doctor* or *nurse*) in different language conditions.

## Introduction

The default use of masculine morphology to refer to non-male entities, often referred to as the ’ambiguous masculine’ or ’masculine generic’, is common amongst both natural and grammatical gender languages [1]. Its use is relatively widespread and can be seen across various language families, including Romance languages (Spanish, French, and Italian), Germanic languages (Dutch, German, and English), Semitic languages (Arabic and Hebrew), and many more. It is often used to refer to someone with unspecified gender (i.e., where there is ambiguity or a need to refer to a person whose gender is unknown) or to refer to a mixed-gender group. Further, its historic use (cross-linguistically) was largely seen as unproblematic and often used for efficiency [2].

Recently however, there has been a surge in the literature exploring the implications of the use of masculine generics on the representation and perception of women in gender-marked languages such as French, German, Dutch and Italian. These studies have provided ample evidence that grammatical gender plays a major role in mediating gender expectations and representation [3–5]. Specifically, these studies have consistently shown that the generic use of masculine grammatical gender results in an over-representation of men and under-representation of women in perception. Studies have also shown that the effect of grammatical gender on perception is strong enough to exhibit ‘carryover effects’ into another language [6–10].

Thus far this research has been relatively limited to ‘Western’ contexts. This study aims to extend this research on grammatical gender and to test whether masculine generics in other language families, specifically Arabic, behave similarly to Indo-European languages. Arabic is one of the most spoken languages around the world, and yet research on the processing of Arabic grammatical gender remains relatively understudied. Additionally, the use of masculine generics in Arabic speaking countries, especially in the context of job recruitment and formal settings, is largely unquestioned and widely accepted as equally representative of all genders. However, a recent study on the language used in Egyptian job recruitment and advertising showed an overuse and inconsistent use of masculine generics, where stereotypically male-dominated industries used masculine generics and stereotypically female-dominated jobs were advertised in feminine grammatical gender regardless of the gender targeted for the role [11]. Additionally, the study showed that jobs were advertised in both singular (majority) and plural masculine generics, and so a key aspect of this investigation is to determine whether masculine generics in singular or plural are interpreted more or less strongly as male-referring. Therefore, the overall aim of this study is to explore how the presence or absence of grammatical gender affects gender representation in perception.

Specifically, the primary objective of this study is to investigate the role that morphological gender marking plays in either entrenching or perhaps mitigating these segregated and polarised recruitment patterns. To do so, we explore the following questions:

1. How does grammatical gender mediate referent expectations in the presence of competing social information?
a. Do singular masculine generics create a male bias in perception, and are these biases different in singular and plural masculine generics?b. Do participants rely more on stereotypical social information or grammatical information to inform their occupational expectations?c. If the social and grammatical cues conflict, do participants exhibit processing costs? Or is there a processing benefit to having congruent social and grammatical cues? And are these benefits or costs consistent across different gender and cue-type combinations?

Additionally, a secondary objective of the study is to develop an understanding as to what kind of language is more likely to promote the retrieval and use of feminine-inflected words and provide a more gender-inclusive interpretation of language. Here we shift our focus to explore the effect of gender-inclusive and gender-neutral language on occupational expectations. To do so, we experimentally test the potential value of using gender-inclusive language as an alternative to default masculine generics to increase women’s representation in cognition by exploring the following questions:

2. Can gender-fair language mitigate gendered expectations and increase the representation of gender minorities?3. Is gender-neutral language interpreted as such? Specifically, do social gender biases and stereotypes persist, in English, despite the absence of grammatical gender marking?

The third and final aim is to explore some of these effects from a bilingual perspective. Here the study explores whether a subsample of Egyptian bilingual participants exhibit any grammatical gender carry over effects from Arabic in their processing of English gender-neutral language. To do so, we explore the following question:

4. Do English monolinguals and Egyptian bilinguals differ in their gender expectations and reliance on stereotypical information? If yes, do Egyptian Arabic/English bilinguals show effects of transferring their knowledge of Arabic grammatical gender to English?

## Theoretical framework

In this section we outline the necessary background information required to contextualise the results, understand the importance and use of this research, as well as our epistemological approach to experimental design.

### How does Egyptian Arabic do gender?

Egyptian Arabic, a diglossic variation of Modern Standard Arabic (MSA), follows the same grammatical gender system as MSA. For the purpose of this experiment, there are no distinctions made between these two variants as role nouns and occupations are consistent across both.

Arabic follows a two-gender system with masculine [+masc] and feminine [+fem] distinctions, and importantly does not possess a ’neuter’ gender option. Similar to Indo-European languages with such a two-gender system (e.g., Spanish), the generic, unmarked, or default form which can be grammatically used to refer to women and men is the masculine. This masculine generic form is typically marked with no overt gender morphology. The feminine form, which is derived from the masculine, is syntactically marked using various morphemes, typically ‘*a(t)’* or ‘*a(h)’*. For animates (humans and various animals), gender assignment is based on semantic information (this information is often the biological sex of the noun) [12]. An example of this can be seen in (1) and (2) below where the ’ *a(h)*’ morpheme is used to transform the masculine noun into feminine. Importantly, this same relationship is also extended to the plural versions of these nouns. It is worth noting that plural masculine generics, relative to their singular counterparts, may be easier to interpret as a mixed-gender group. Despite being more overtly marked, the use of masculine plurals to refer to women in speech is not uncommon (e.g., *nurses* [+masc] to refer to a group of women), whereas the singular masculine would be uncommon in speech.

(1)مدرسmudaresteacher.M.SG’teacher[+masc]’(2)مدرسةmudares-**ah**teacher.F.SG’teacher[+fem]’

While this nominal agreement pattern is similar to many Indo-European languages, unlike Spanish, French, German, etc., Arabic requires gender and number agreement across pronouns, verbs, nouns and adjectives at the inflectional phrase level [12]. Consequently, gender marking is more salient and reinforced in Arabic than Spanish or German. Consequently, adopting gender-inclusive language in Arabic can be more costly and effortful as it would require a large amount of repetition to avoid the use of masculine generics.

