### Definitions

In this section we operationalise the definitions and terms to be used throughout this study. Firstly, a key distinction is made throughout this study between grammatical gender (G-gender) and social gender (S-gender). G-gender explicitly refers to the morphology, whereas S-gender indicates a referent, person, or occupational gender expectation. For example, using the masculine generic to refer to a group of *nurses* in Arabic will have masculine G-gender, but social expectations may (or may not) result in a different S-gender interpretation. Importantly, where G-gender information is insufficient or absent, reliance on S-gender information may be utilised to determine the gender of a referent. Additionally, G-gender and S-gender information may be congruent/incongruent, which may induce processing benefits or costs. For example, it may be easier to interpret *engineer* [+ masc] as a man and *nurse* [+fem] as a woman than the other way around. This is because S-gender is typically determined by an individual’s expectations or stereotypical information and is likely to vary due to different socio-cultural backgrounds and personal experiences.

Secondly, when describing a ’male-bias’ in this study, this refers to an over-representation of male referents compared to female referents. Specifically, occurrences of *strict* male interpretations of masculine G-gender, which in principle refers to all S-genders will be considered a male-bias in perception/interpretation. This is to be distinguished from cultural and social biases or attitudes individuals may hold that cannot be attributed to G-gender. Additionally, this male-bias can manifest itself in processing benefits or costs due to violations/confirmations of S-gender expectations (e.g., processing benefits experienced when G-gender is congruent with S-gender (as in *doctor[+masc]* and *nurse[+fem]*) and processing costs when G-gender is incongruent with S-gender (i.e., *doctor[+fem]* and *nurse[+masc]*).

Thirdly, in this study, the term ’number’ always refers to grammatical number (e.g., singular, dual, or plural) unless otherwise stated.

A final note on social gender: during this study binary interpretations of S-gender are more common given the sociocultural background in Egypt, where nonbinary identities are unrecognised and marginalised in formal and informal contexts.

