The second component is considered an exploratory sub-experiment of the first which evaluates the effect of plural masculine generics on the occupational expectations of Egyptian Arabic speakers. The key difference between this component and the former is that this block does not test this relationship in other language conditions (such as feminine plurals or in binomial word-pairs) which would require 3 additional blocks instead of one. This component will be used to explore one key question: do plural masculine generics and singular masculine generics elicit the same male-bias in representation? Importantly, this exploratory sub-experiment has 6 experimental stimuli (in the masculine) compared to the other blocks (see Table 3). This is to ensure a balance of masculine and feminine priming throughout the experiment.

**Table 3 pone.0292936.t003:** Experimental block for the plural masculines.

Block	Male Stereotype	Female Stereotype	No Stereotype
**Block 4**	**مديرين** **Managers [+ masc]**	راقصة Dancer [+ fem]	تلميذة/تلميذ Student [+ fem/masc]
	محامية/محامي Lawyer [+ fem/masc]	**ممرضين** **Nurses [+ masc]**	مسؤولة مبيعات Salesperson [+ fem]
	دكتورة Doctor [+ fem]	**مضيفين طيران** **Flight Attendants [+ masc]**	**ممثلين** **Actors [+ masc]**
	**مهندسين** **Engineers [+ masc]**	عاملة نظافة Cleaner [+ fem]	**مغنيين** **Singers [+ masc]**

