### Outcomes of interest

To answer the research questions outlined above, the study focuses on two outcome categories: fluency measures and the participant’s gender interpretation of the prime.

Fluency measures consist of 5 dependent variables: the total number of words produced, hesitation markers, number of false starts, fluency mistakes, and initial response time. These measures are consistent with current literature on speech production [34]. The focus on fluency allows for exploration of processing costs and benefits due to in/congruent or asymmetric stimuli. Additionally, fluency measures help show what is easily accessed or recalled. Processing benefits are expected when participants’ S-gender expectations are not violated (i.e., a *secretary* in feminine morphology and a *manager* in masculine morphology compared to a *secretary* in the masculine). Importantly however, roles associated with women presented in masculine morphology should *not* result in processing costs if masculine G-gender is truly interpreted as generic or unmarked.

To measure the participant’s interpretation of the prime their responses will be coded based on the proportion of gendered morphosyntactic markers in their speech. Importantly, this will be weighted at the tensed phrase (TP) level. This is to avoid inflating scores based on morphosyntactic markers for the sake of agreement across noun phrases or verb phrases. This coding will be used to derive two other categorical variables to be used in the analysis: the participant’s gender expectations and whether the expectations are congruent with the social stereotype associated with the prime.

Example 3 provides a fictitious response to the stimulus “*manager [+masc]*” and how this would be coded. Firstly, we can see that there are three morphosyntactic markers that are masculine, two of which are used only for agreement purposes. Secondly, we can determine that the participant interpreted the stimulus to be a man and that this response is congruent with the prime (i.e., grammatical gender and social gender are not asymmetric).

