For conditions with strict masculine or strict feminine G-gender: regardless of role stereo-typicality participants’ responses will be determined by the G-gender of the prime. In other words, the priming effect of G-gender will overpower the priming effect of social stereotype information and participants will strictly rely on G-gender rather than stereotype information to determine the S-gender of the referent. Further, this relationship will be more extreme in the singular compared to the plural (as the singular is less likely to be interpreted as generic compared to the plural). Consequently, it is expected that masculine generics will result in a male bias in perception and interpretation. Similarly, feminine G-gender **should** also result in female interpretation as this cannot be used generically. Importantly, if the masculine and feminine conditions behave similarly, this will confirm the notion that masculine generics are not actually generic in interpretation and are instead gender exclusive.

Further, it is expected that the neutral roles in the masculine generic condition will be more readily interpreted as stereotypically male and may also act as a ‘congruent’ condition. Therefore, participants’ responses towards ‘neutral’ roles (such as *student*) will mirror responses towards male-dominated roles.

In condition 3 (inclusive language), it is unclear how participants will interpret the stimuli. Firstly, due to the presence of gender-fair language, we would expect participants to use both feminine and masculine morpho-syntactic markers across all roles, with the neutral stereotype condition being the most compatible with this behaviour. In this scenario, participants will have shown that gender inclusive language can be used to overcome male bias in perception and increase the retrieval of female exemplars. Alternatively, participants’ gender expectations and interpretation of the prime may instead be determined by social stereotype information. In this case, we can determine that despite the presence of a feminine morphosyntactic marker in the stimulus and an increase in accessibility of female exemplars, gender inclusive language does not increase the retrieval of female exemplars in the presence of competing social stereotype information (i.e., a failure to overcome gender bias in perception because of social expectation).

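### The marker-share outcome is a weaker measure of a strictly male reading in the plural than in the singular, which biases the singular-plural comparison against the predicted ordering

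*Protocol article*

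**What the plan says.** All references are to the protocol article.

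- **Target of inference.** The Definitions section separates grammatical gender from the gender of the referent. It counts as male bias "occurrences of *strict* male interpretations of masculine G-gender". The target is who the speaker has in mind, not the form used.
- **Measurement.** Under Outcomes of interest, "their responses will be coded based on the proportion of gendered morphosyntactic markers in their speech". It continues: "This coding will be used to derive two other categorical variables to be used in the analysis". One of the two is the participant's gender expectation. The worked example is a singular, and its masculine markers are read as a man. The one stated adjustment is weighting at tensed-phrase level, so that agreement does not inflate the score.
- **Usage.** The section on how Egyptian Arabic marks gender says that "the use of masculine plurals to refer to women in speech is not uncommon", giving the masculine plural of nurse for a group of women, "whereas the singular masculine would be uncommon in speech". It adds that plural masculine generics may be easier to read as a mixed group.
- **Comparison.** The second component (block 4, Table 3) has one key question: "do plural masculine generics and singular masculine generics elicit the same male-bias in representation". It is labelled exploratory. The Introduction calls it a key aspect of the investigation and makes it half of question 1a.
- **Prediction.** The Hypotheses section expects that "this relationship will be more extreme in the singular compared to the plural".

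**The concern.** On the plan's own account, the link from marker to referent depends on number. A speaker thinking of women, or of a mixed group, may well speak in the masculine plural but would seldom use a masculine singular. The coding as stated treats a masculine marker the same way in both numbers. Some non-strict readings of a plural prompt would then be scored as male, and few readings of a singular prompt would be.

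This is misclassification that differs between the two arms of the comparison. It raises the apparent male share in the plural, where the plan expects more generic readings. An equal or higher masculine share in block 4 could then be reported as the same or stronger male bias when it reflects only how plurals are used.

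**Working it through.** **Inputs.** The documents give no rate for masculine marking of non-male referents in either number, and no expected male shares. There is no figure in the plan to reproduce on this point, and every value below is an assumption.

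**Model.** For each number, let p be the true share of strictly male readings, and g the probability that a non-male reading (women or mixed) is voiced in masculine markers and so coded male. Male readings are taken as always coded male. Subscript s is singular, p is plural.

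- Observed masculine share = p + (1 - p)g
- Observed gap = [p_s + (1 - p_s)g_s] - [p_p + (1 - p_p)g_p]
- The observed order reverses when g_p > 1 - (1 - p_s)(1 - g_s)/(1 - p_p)

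**Scenario A: p_s = 0.90, p_p = 0.50, true gap +40 points.** The observed singular share is 0.90 at g_s = 0, and 0.90 + 0.10 × 0.10 = 0.91 at g_s = 0.10. The observed plural share is 0.50 + 0.50 × g_p.

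| g_p | Plural share | Gap, g_s = 0 | Gap, g_s = 0.10 |
|---|---|---|---|
| 0.1 | 0.55 | +35 | +36 |
| 0.2 | 0.60 | +30 | +31 |
| 0.3 | 0.65 | +25 | +26 |
| 0.4 | 0.70 | +20 | +21 |
| 0.6 | 0.80 | +10 | +11 |
| 0.8 | 0.90 | 0 | +1 |
| 1.0 | 1.00 | -10 | -9 |

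The reversal threshold is 1 - 0.10 × 1.00/0.50 = 0.80 at g_s = 0, and 1 - 0.10 × 0.90/0.50 = 0.82 at g_s = 0.10.

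**Scenario B: p_s = 0.80, p_p = 0.60, g_s = 0.05, true gap +20 points.** The singular share is 0.80 + 0.20 × 0.05 = 0.81. The plural share is 0.60 + 0.40 × g_p, so g_p = 0.1, 0.3, 0.5, 0.7 and 0.9 give gaps of +17, +9, +1, -7 and -15 points. The threshold is 1 - 0.20 × 0.95/0.40 = 0.525. Over p_s of 0.7-0.9, true gaps of 10-30 points and g_s of 0-0.10, thresholds run from 0.25 to 0.775.

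**Role of the asymmetry.** If g is equal in both numbers and below 1, the observed gap is (p_s - p_p)(1 - g): smaller, but never reversed. Reversal needs g_p above g_s, which is the direction the plan's usage remark describes.

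**What a result in the predicted direction would mean.** The observed non-masculine share is (1 - p)(1 - g). If g_p is at least g_s and the singular is observed as more masculine, then (1 - p_p)(1 - g_p) > (1 - p_s)(1 - g_s), which forces p_p < p_s. This error cannot produce a false result in the predicted direction.

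**Does any stated rule repair it?** Tensed-phrase weighting removes repeated agreement within a phrase. It does not say whether a masculine plural refers to men, women or both.

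**The case against.** Several points on the other side have force.

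- **The text is mild.** It says not uncommon, and no rate follows from that. In scenario A, plural rates of 10-30% leave a gap of about +25 to +36 points. This stands: the size is open.
- **Responses need not be plural.** The task is to produce as many related words as possible. The rule that "Arabic requires gender and number agreement across pronouns, verbs, nouns and adjectives" is stated for the inflectional phrase, not between prompt and response. A participant who describes one exemplar in the singular escapes the problem. This stands as a condition on the finding.
- **The article is condensed.** A fuller coding scheme may treat plurals separately, and the authors do allow for mixed readings, though only for the word-pair condition. This limits the claim to what is stated: one coding principle, with no distinction by number.
- **Marker share is not the only outcome.** The plan says male bias may also show as processing costs, and fluency does not depend on what a masculine plural refers to. This stands, but fluency supplements the marker comparison and does not correct it.
- **The comparison is exploratory and the bias is conservative.** Both are true. The harm is confined to a null or reversed result, but such a result would be read as an answer to block 4's key question.

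A reader might infer that at least half of the true difference will be lost, or that the result will reverse. The documents do not support either. The first needs an assumed plural rate of about 40% or more in scenario A, and the second a rate above about 80% there.

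**Conclusion.** The concern holds as a validity problem of known direction and unknown size. Where responses to plural prompts are plural, the marker-based outcomes can overstate strictly male readings in the plural relative to the singular, and so work against the predicted ordering. Under scenario A's assumptions a true gap of +40 points is observed as anything from about +36 to -10. Smaller true gaps can reverse at lower plural rates.

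The conclusion rests on the plan's own usage remark, on a coding rule with no stated distinction by number, and on plural responses to plural prompts, which the protocol does not guarantee. It does not touch the fluency outcomes, and it does not undermine a result in the predicted direction. What cannot be read at face value is an equal or higher raw masculine share in the plural.

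**What to change.** 1. In the description of block 4 and under Outcomes of interest, state that an equal or higher raw masculine share in the plural is not evidence of the same or stronger male bias.
2. Code masculine plural markers as male or mixed, undetermined. Count a strictly male reading only where singular reference or other content of the response makes it unambiguous.
3. Report the singular-plural contrast with a sensitivity analysis over a stated range of masculine marking for non-male plural referents, alongside the fluency contrast.

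**Cost.** The first item costs nothing. The second adds a coding rule, and fewer plural responses will classify as strictly male, so the contrast is less precise. The third adds one analysis.

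**What not to do.** It is tempting to turn some of block 4's feminine singular prompts in Table 3 into feminine plurals and use them as a reference rate. That would not estimate the rate needed. They would measure marking after a feminine prompt, which the Hypotheses section itself expects to drive the response. The nouns now shown in the feminine in block 4 (dancer, salesperson, doctor, cleaner) are not those shown as masculine plurals, and the prompts would cover all-female groups only. Table 3 should stay as it is on this point.
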